#### Social level outcomes

##### Perception of peers physical activity and healthy eating

To assess perception of peers' physical activity, we will use a questionnaire developed as part of the Trial of Activity for Adolescent Girls (TAAG) (61). The questionnaire asks participants to identify their three closest friends and, for each friend, answer six items about their experiences engaging in physical activity with the friend. A second questionnaire, based on the TAAG questionnaire, was developed to assess the perception of peers' healthy eating behaviors. For both surveys, five items are yes/no response variables, and each item's score reflects the number of friends for which the item is answered in the affirmative. Additionally, one item assesses the frequency of physical activity with each friend with a 5-point ordinal scale ranging from never to five or more times per week. A total score will be calculated across all items for each behavior, with higher scores representing higher levels of perceived peer engagement in physical activity or healthy eating.

#### Environmental level outcomes

##### Participant perception of school health environment

We will assess students' Perceptions of the Environment and Patterns of Diet at School (PEA-PODS) using a validated survey (62). The PEA-PODS survey is 40 items scored on 5-point Likert scales, and it includes questions about students' perceptions of physical activity and nutrition policies and practices (11 items), teacher wellness policies and practice (16 items), cafeteria policies and practice (7 items), and recess policies and practices (6 items). Each subscale will be scored individually, and items will be aggregated across constructs to create an overall score (higher scores related to a better perceived environment).

##### School environment assessment

School staff will provide an assessment of the school health environment by completing a School Physical Activity and Nutrition Environment Questionnaire (63). The questionnaire includes three parts—administration, physical education, and food service—and each part will be filled out by the most knowledgeable person on each topic. However, if a school staff member serves in two of the previously mentioned positions, they may fill out the survey once for both positions. For the administration portion of the survey, 24 questions ask about school health advisory councils, parent-teacher organizations, school-wide participation in physical activity or nutrition initiatives, sharing of health information with parents, as well as general food and nutrition policies for the school. For the physical education portion of the survey, 33 questions evaluate the frequency and content of physical education, active commuting to school programs or opportunities, availability of physical activity facilities and policies, fitness assessments and reporting, and organized sports and physically active clubs. Finally, the food services portion of the survey uses 20 questions to assess policies and practices at breakfast and lunch, participation in federal meal programs, and foods that are available on campus throughout the school day.

##### Photovoice

We will qualitatively measure changes in students' perceptions of the school food and physical activity environment using a photovoice approach. Photovoice is a participatory research method where participants use photography and storytelling to document and reflect on their experiences (64), which we have embedded as an activity in the STHS curriculum as part of STHS module three (initial assessment) and module 15 (reassessment). For module three, participants will also identify an environmental change to make as part of their STHS project, and for module 15, they will reflect on environmental changes that have occurred in their school over the course of the program. All students will be anonymized and participate in the photovoice data collection sessions, regardless of consent/assent to participate in the STHS study.

To conduct the photovoice session, we will divide students into 3–5 students per group and instruct each group to assess the food environment or the physical activity environment, with at least one group per school assessing each of the two environments. Each photovoice session will consist of a walkabout to take pictures of the school environment (15–20 min) and the selection of one photo per group to answer questions during an implementer-moderated class discussion (15–20 min). For the walkabout, we will provide each group with an instant print digital camera and instruct participants to build consensus on which features of the school food and physical activity environment to capture. Participants will also have a worksheet to complete after the walkabout, instructing them to note supportive or challenging features in their food or physical activity school environment. Following the walkabout, participants will reconvene in the classroom and use a worksheet with guiding questions, build consensus within their group on selecting one picture to share as part of the moderated discussion with all groups. The worksheet questions are informed by the SHOWeD process, an established methodological approach to photovoice previously used in middle school settings (65–68). The SHOWeD questions facilitate contextualization and exploration of root causes surrounding the photographic image captured by participants. The implementer will then facilitate a class discussion using the same SHOWeD process questions to generate a collaborative discussion.

We will audio-record and take structured observations on all phases of the process (walkabout, picture selection, and discussion). Additionally, we will debrief as a team following each photovoice session, noting the degree of group engagement and consensus-building that occurred during the session, and summarizing the prevalent discussion points among participants.

### Data analysis

#### Sample size

As abdominal obesity is a necessary component of MetS, we powered this study on between-group changes in obesity. Based on the existing literature, we set an alpha of 0.05 and estimated a within-school intraclass correlation coefficient of 0.025 to account for cluster effect, an effect size of *d* = 0.27, and an effect size variability of 0.07. As a result, we will need to recruit 20 participants per school to achieve 80% power to detect a statistically significant change in abdominal obesity between the intervention and control group participants. Previous school- and community-based studies have shown similar effect sizes for changes in obesity-related outcomes (69–72). We will aim to recruit 25 students per school to ensure that we have 20 students available for measures, given that the normal retention rate is 80% in community-based research. We anticipate low participant attrition given that the school setting provides a controlled environment where consistent attendance is expected and buy-in from school administration and teachers often leads to higher student engagement and accountability (73). Furthermore, we will be working with Extension agents who often have strong community ties, fostering trust and rapport with students and families (74).

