## Introduction

Metabolic syndrome (MetS) is a cluster of risk factors that increases an individual's risk for cardiovascular disease and type 2 diabetes (1). These risk factors can appear early in childhood, leading to lifelong chronic disease morbidity and mortality (2, 3). A diagnosis of pediatric MetS, following the International Diabetes Federation (IDF) criteria and modified to meet appropriate pediatric thresholds, requires the presence of abdominal obesity plus at least two of the following risk factors: hyperglycemia or insulin resistance, hypertension, elevated triglycerides, or low levels of high-density lipoprotein (4). In the United States, MetS risk factors are increasingly evident earlier in life and affect races and ethnicities disproportionately (5, 6). Among adolescents aged 12 to 19 years, 10.1% have MetS, and 73.2% have at least one condition related to MetS (5). Among overweight adolescents, one in three is affected by MetS (7). Cardiometabolic risk factors, such as obesity and type 2 diabetes, are more prevalent among adolescents who identify as African American/Black and Hispanic/Latino compared to their White counterparts (8).

Early prevention and treatment of MetS, through the promotion of healthy lifestyle behaviors, is essential for reducing the incidence of cardiovascular disease and type 2 diabetes throughout life (9, 10). Diet quality and physical activity are two healthy lifestyle behaviors closely linked to MetS (11). However, among adolescents, 66% exhibit poor diet quality, and only 8% meet the recommended 60 min of physical activity per day, with a smaller proportion of African American/Black and Hispanic/Latino adolescents adhering to dietary and physical activity recommendations (12, 13). Interventions that promote physical activity and healthy eating behaviors are needed to reduce MetS and improve the health of children and adolescents.

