### Measures

All student participant outcomes will be measured for student participants at both the intervention and delayed intervention control group schools within 1 month of the student recruitment period (T1), at the end of the school year or intervention period (T2), at the start of the next school year (T3), and at the end of the next school year (T4; Figure 1). Data collection sessions are estimated to take 45 minutes per student, and measures will be administered to students as a group. The two primary individual-level outcomes for this study are changes in MetS and positive youth development. Secondary individual-level outcomes include: (1) individual metabolic risk factors (blood pressure, fasting blood glucose, waist circumference, HDL cholesterol, and triglycerides); (2) body mass index percentile; (3) fruit and vegetable consumption; (4) accelerometer-derived physical activity, sedentary time, and sleep; and (5) cardiorespiratory fitness. Finally, other outcomes we will survey include TPB constructs related to nutrition and physical activity, nutrition- and physical activity-related behaviors, and youth's engagement with the school health environment. At the social level, we will assess students' perceptions of their peers' physical activity and healthy eating. At the environmental level, we will: (1) measure students' perceptions of the school health environment; (2) have school administration and staff complete a school environment assessment; and (3) conduct photovoice sessions. Student participants in both the intervention and the delayed intervention control group will receive a $50 gift card for each data collection session they complete (T1 to T4; $200 maximum for completing all sessions).

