#### Individual-level outcome measures

##### Metabolic syndrome

Participants' MetS will be categorized dichotomously (yes or no) using the IDF definition of MetS for children and adolescents aged 10 to < 16 years old—abdominal obesity plus at least two of the four other MetS risk factors. The IDF uses the following criteria to define risk for each component: (1) waist circumference >90th percentile (i.e., abdominal obesity); (2) systolic blood pressure >130 or diastolic blood pressure >85 mmHg; (3) triglycerides >150 mg/dl; (4) high-density lipoprotein cholesterol (HDL-C) < 40 mg/dl; and (5) fasting blood glucose >100 mg/dl (45). Each risk factor will also be analyzed individually as a continuous variable as a secondary outcome.

Waist circumference will be measured using a medical-grade tape measure with Gulick spring attachment, and it will be measured at the midpoint between the floating rib and iliac crest. The measure will be performed three times and an average of the two closest measures will be used. Blood pressure will be measured using an automated Omron sphygmomanometer and an appropriately sized cuff on the children's upper right arm. As needed, participants will be asked to remove or pull up any bulky garments covering their upper right arm before testing begins. Participants will be asked to remain seated for 5 min before the measurement is taken. Blood pressure will be measured three times, and the two closest measurements will be averaged. For glucose, HDL-C, and triglycerides, participants will be directed to complete an overnight fast. A single capillary blood sample will be collected and inserted into a portable CardioChek Plus analyzer to measure triglycerides, HDL-C, and glucose. Only one measurement will be collected.

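### The sample size rests on a standardised obesity effect, and that power does not carry over to the yes/no MetS diagnosis or to positive youth development, the two primary outcomes

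*Protocol article*

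**What the plan says.** The Measures section states: "The two primary individual-level outcomes for this study are changes in MetS and positive youth development". Under Metabolic syndrome, "MetS will be categorized dichotomously (yes or no) using the IDF definition": abdominal obesity plus at least two of four other risk factors. The components enter separately and lower in the hierarchy: "Each risk factor will also be analyzed individually as a continuous variable as a secondary outcome".

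The Sample size section says "As abdominal obesity is a necessary component of MetS, we powered this study on between-group changes in obesity". Its inputs are d = 0.27 and "we set an alpha of 0.05 and estimated a within-school intraclass correlation coefficient of 0.025", "and an effect size variability of 0.07", and 20 students per school for 80% power. The power claim is worded for abdominal obesity.

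The Quantitative analysis section tests between-group differences in post-intervention MetS and positive youth development in a generalized linear model, with the baseline value as a covariate. The Introduction gives the only overall MetS prevalence: "Among adolescents aged 12 to 19 years, 10.1% have MetS".

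**The concern.** That MetS cannot be diagnosed without abdominal obesity makes the MetS cases a subset of the abdominally obese. It does not make power for one into power for the other. A smaller waist changes the diagnosis only in a student who crosses the waist threshold and also has at least two other abnormal factors. A shift in a mean and a change in the frequency of a composite diagnosis are different quantities, with different standard errors. The obesity calculation also says nothing about the youth-development score.

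The stake is how the result will be read. The trial is presented as a test of efficacy for reducing MetS risk and carries an 80% power statement. A null result on the diagnosis could be taken as evidence that the programme does not work, although a null would be the likely result even if an effect of the adopted size were real.

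**Working it through.** **Inputs.** 20 schools (Design); 1:1 allocation (Randomization); 20 analysed per school, ICC 0.025, d = 0.27, alpha 0.05 (Sample size; taken as two-sided); MetS prevalence 10.1% (Introduction; 5% to 20% assumed as a range).

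Per arm: 10 × 20 = 200. Design effect: 1 + (20 − 1) × 0.025 = 1.475. Effective n per arm: 200 / 1.475 = 135.6. Degrees of freedom: 20 − 2 = 18, critical t = 2.101.

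**1. The plan's own figure.** For a standardised mean difference, SE = √(2 / 135.6) = 0.1214 and the noncentrality is 0.27 / 0.1214 = 2.22. Power is 56% (t, 18 df) or 60% (normal), not 80%. A baseline correlation r multiplies the variance by (1 − r²). Power is then 68% at r = 0.5, 75% at 0.6, 79% at 0.65 and 84% at 0.7. The article states no such correlation. This is a separate matter, but it limits what the fix can promise.

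**2. Carrying d = 0.27 to the yes/no scale.** The protocol gives no MetS effect, so this step is an assumption, made in two ways.
- Logistic: OR = exp(−0.27 × π / √3) = 0.613. Odds 0.101 / 0.899 = 0.1123; 0.1123 × 0.613 = 0.0688; p₁ = 0.0688 / 1.0688 = 6.4%.
- Latent normal: p₁ = Φ(Φ⁻¹(0.101) − 0.27) = 6.1%.

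**3. Power for the diagnosis at 10.1%.** SE = √[(p₀q₀ + p₁q₁) / 135.6].
- Logistic: √[(0.0908 + 0.0603) / 135.6] = 0.0334; noncentrality (0.101 − 0.0644) / 0.0334 = 1.10; power 18%.
- Latent normal: SE 0.0331; noncentrality (0.101 − 0.0611) / 0.0331 = 1.21; power 21%.

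**4. Range (t, 18 df, no baseline adjustment).**

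| Control prevalence | d-equivalent, logistic | d-equivalent, latent normal | MetS halved |
|---|---|---|---|
| 5% | 11.5% | 15% | 18% |
| 10.1% | 18% | 21% | 32% |
| 15% | 24% | 25% | 46% |
| 20% | 29% | 29% | 60% |

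From 10.1%, 80% power needs a fall to about 1.7%, a relative reduction of about 83%.

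**5. Sensitivity at 10.1%.**
- Baseline adjustment treated as a variance reduction, r = 0.5 to 0.7 (assumed): d-equivalent power is 22% to 31% (logistic) or 26% to 36% (latent normal); halving gives 41% to 55%.
- ICC: if 0.025 is a latent-scale value, the observed-scale ICC is about 0.009, the design effect about 1.17 and power about 21% to 25%. With no clustering at all, power is still under 30%.
- Cases: 400 × 0.101 ≈ 40 with no effect; 20.2 + 200 × 0.0644 ≈ 33 with the logistic effect.

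**The case against.** The protocol calls this a pilot that will give initial evidence, and it says openly that power concerns abdominal obesity; it claims none for MetS. An analysis plan that is not shown may add detail. All of this is fair and bears on severity. It does not repair the stated rationale, which infers adequacy for MetS from obesity, and the same text sets out to test efficacy on MetS.

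A reader might infer that the trial simply has 20% power for MetS. The documents do not support a flat figure. The MetS effect is assumed, and 10.1% is a national rate for ages 12 to 19, whereas the sample is grades 5 to 8 in schools with a high share of Black or Hispanic students. Younger age points to a lower rate and higher risk to a higher one. Even at about 33%, roughly the Introduction's figure for overweight adolescents, d-equivalent power is only 35% to 40%.

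Two further inferences also fail. One is that baseline adjustment recovers almost nothing: the values above show a visible but insufficient gain. The other is that the model would be unstable with 20 clusters: the protocol names only a generalized linear model framework with district as the clustering variable, so neither the number of clusters nor any instability is established.

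Replacing a recognised diagnosis with a score also changes the question asked. That is a real cost.

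**Conclusion.** The mismatch stands on the text alone: the outcome behind the power claim is not a primary outcome, and the link offered between them is not valid. The size is conditional. With an assumed effect equivalent to d = 0.27, 10.1% prevalence, 200 analysed per arm, ICC 0.025 and t on 18 df, power for the diagnosis is about 20%. Varying the prevalence or the baseline adjustment within the ranges shown leaves d-equivalent power well below 80% for prevalences up to 20%. Higher power needs a much larger effect: halving MetS from 20% gives about 60% unadjusted, and more with strong baseline adjustment. Confidence is high in the mismatch and moderate in any single power figure.

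**What to change.** - **Sample size:** remove the inference from abdominal obesity to MetS, say that the power statement concerns obesity only, and give the detectable difference or expected confidence-interval width for each primary outcome, with the assumed prevalence, ICC and baseline correlation.
- **Measures and Metabolic syndrome:** make the primary MetS measure a prespecified continuous risk score, for example the mean of age- and sex-standardised waist, blood pressure, triglycerides, inverse HDL-C and glucose. Analyse it by ANCOVA on its own baseline, allowing for clustering. Keep the IDF diagnosis as secondary, with a confidence interval and no power claim.
- **Timing:** lock and register the change before anyone sees outcome data by arm. The study team learns each school's assignment, so a change made merely before the formal analysis would not be safe enough.

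The cost is a protocol and registry amendment; no new data are needed. A score is less directly clinical than a diagnosis. Its power for d = 0.27 is about 56% unadjusted and reaches 80% only with a baseline correlation above about 0.65, so 80% should not be claimed for it without stating that assumption. If the diagnosis is kept as primary, the first change is still needed.

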## Methods and analysis

### Design

We will recruit two cohorts of schools (*n* = 20 schools, total) to participate in a 9-month pilot cluster randomized controlled trial. The study design processes—including school recruitment, enrollment, and randomization, as well as student recruitment, data collection timepoint, and program participation—are illustrated in Figure 1 and described in detail below. Once a school agrees to participate, it will be randomized to receive the STHS intervention immediately or a delayed intervention condition (i.e., control group). The delayed intervention group will receive the curriculum to implement at their discretion, one school year after serving as a control. We will collect pre-(beginning of the academic year; T1) and post-test outcomes (end of the academic year; T2) for intervention and delayed intervention conditions. Additionally, for the intervention group, we will gather outcomes at 4 months (T3) and 12 months (T4) post-intervention to assess the short- and long-term maintenance of the intervention effects. The trial has been registered on clinicaltrials.gov (NCT05867433). The Institutional Review Board at Texas A&M University approved all measures, procedures, and protocols (IRB2023-0530D).

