### Selection of subjects

#### Recruitment

School recruitment will occur using a two-pronged approach. First, we will use the Texas Education Agency website to identify contact information for all middle schools in Texas that meet inclusion criteria (38). We will recruit schools using emails, phone calls, and information folders dropped off at eligible schools in Texas. Simultaneously, we will work with AgriLife Extension Family and Community Health and 4-H agents to identify schools that may be interested in participating in the study. We will hold in-person or virtual meetings with school representatives (e.g., school health advisory councils) to provide an in-depth program description. School administrators from all schools that enroll in the study will sign a memorandum of understanding (MOU) agreeing to participate.

Within schools, we will recruit 5th through 8th grade students (*n* = 20–25 students per school). Eighth-grade students will only be recruited in schools that also have an attached high school where eighth-grade students matriculate, so that they can be assessed at follow-up. Otherwise, we will not recruit 8th-grade students because their transition into high school could introduce new individual and/or environmental factors that may affect study outcomes. Likewise, we will only recruit 5th through 8th grade students from elementary schools if the grade does not matriculate into another school the following year. We will disseminate information for participating in the STHS program via school-wide announcements, flyers posted at the intervention schools, and school-sponsored events. Students and their parents will also receive an email with information about participating in the research study and information on how to contact the research team if they are interested in their student(s) participating. We will also host information sessions for parents and students before and after school, where they can ask more questions about the program. Prior to signing consent forms, the research team will screen participants for inclusion and exclusion criteria. If the student qualifies for the study, the parent will be asked to read and return a consent form. Students will be asked to assent to participate in all study procedures.

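### The stated 80% power does not follow from the stated inputs: 10 versus 10 schools of 20 students, ICC 0.025 and d = 0.27 give about 56–60% before any baseline adjustment

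*Protocol article*

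**What the plan says.** The Sample size section of the protocol article bases power on obesity, because abdominal obesity is a required component of metabolic syndrome. It gives four inputs: "we set an alpha of 0.05"; it "estimated a within-school intraclass correlation coefficient of 0.025 to account for cluster effect"; and it takes "an effect size of *d* = 0.27, and an effect size variability of 0.07". It presents the result as following from these: "we will need to recruit 20 participants per school to achieve 80% power to detect a statistically significant change in abdominal obesity". It then sets a target of 25 recruits per school so that 20 can be measured at 80% retention.

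The number of schools is fixed elsewhere. The Design section begins "We will recruit two cohorts of schools" and gives 20 schools in total. The Randomization section allocates whole schools one to one, so there are 10 per arm. The Recruitment section gives "20–25 students per school". The Quantitative analysis section includes the baseline score as a covariate.

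The article does not state the sidedness of alpha, a baseline–outcome correlation, or what the variability of 0.07 measures.

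**The concern.** A reader can put the listed inputs into the usual formula for a two-arm trial randomising schools, and the answer falls well short of 80%. This is a stated result that does not follow from its stated inputs, so it is not a detail that an article may leave to a fuller document. The article makes a formal power claim for what it calls a test of efficacy, and it links larger studies and dissemination to the findings. Readers are told that the chance of missing the planning effect is 20%. On the printed inputs, without baseline adjustment, that chance is 40–44%. Either an input is missing from the text or the calculation was made for a different design.

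**Working it through.** **Inputs.** From Sample size: alpha 0.05, ICC 0.025, d = 0.27 (outcome SD set to 1), m = 20 students analysed per school. From Design and Randomization: K = 20 schools, 10 per arm. Assumed: two-sided test, equal school sizes, a standardised mean difference, school as the unit of clustering.

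**Attempt to reproduce 80%.**
- Variance of the difference = 4 × (ICC + (1 − ICC)/m)/K = 4 × (0.025 + 0.975/20)/20 = 4 × 0.07375/20 = 0.01475.
- SE = √0.01475 = 0.1214.
- Noncentrality = 0.27/0.1214 = 2.223.
- Power = 60.4% (normal) or 55.7% (noncentral t, 20 − 2 = 18 df).

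The design-effect route agrees: 1 + 19 × 0.025 = 1.475, and 200/1.475 = 135.6 effective students per arm, which gives the same 60.4%.

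**Variants of the stated inputs.**

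| Variant | Normal | t, 18 df |
|---|---|---|
| As stated, two-sided | 60.4% | 55.7% |
| One-sided | 71.8% | 68.9% |
| All 25 recruits retained, two-sided | 66.5% | 61.7% |
| All 25 retained, one-sided | 77.1% | 74.2% |
| ICC set to 0, two-sided | 77.0% | 72.4% |
| 0.07 as between-school variance of the effect in the intervention arm | 44.9% | 41.0% |
| 0.07 as the SD of that effect (variance 0.0049) | 59.0% | 54.4% |

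None reaches 80%. The last two rows add 0.07/10 or 0.0049/10 to the variance, so they can only reduce power.

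**What would give 80%.**
- Effect size at 20 × 20: d = 0.340 (normal) or 0.360 (t).
- Schools of 20 at d = 0.27: 32 (normal, 80.3%) or 34 (t, 80.3%).
- Students per school at 20 schools and d = 0.27: about 59 on the t reference.

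The normal-reference 0.34 equals 0.27 + 0.07, but nothing in the article supports adding the two.

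**Baseline adjustment, with d in raw-outcome SD units.** The noncentrality needed is 1.960 + 0.842 = 2.802 (normal) or 0.3598/0.12145 = 2.963 (t, 18 df). The variance must therefore fall to (0.27/2.802)² = 0.00929 or (0.27/2.963)² = 0.00831.
- If the covariate acts equally at school and student level, R² = 1 − 0.00929/0.01475 = 0.37 (normal) or 1 − 0.00831/0.01475 = 0.44 (t; r about 0.66).
- If it acts at student level only, solve 4 × (0.025 + 0.04875 × (1 − R²))/20 for the same variances. This gives R² = 0.56 (normal) or 0.66 (t; r about 0.81). In that case r = 0.66 gives only 75% (normal) or 70% (t).

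**The case against.** The strongest reply is that the trial will not be analysed unadjusted. The model includes the baseline score, and for a body-size measure the correlation could be high. If r were 0.7 (an assumed value), acting equally at both levels with d in raw SD units, power would be 84% (t) or 88% (normal). This stands as a limit on the conclusion. A reader might infer that the trial has little better than an even chance of detecting its planning effect. The article does not support that, because 56–60% is the unadjusted figure. It does not rescue the printed statement either: no correlation is among the listed inputs, and since the section speaks of between-group changes, d may already be on the change scale with the gain counted.

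A second tempting inference is that the 0.07 has no place in a school-randomised calculation, or shows that the calculation put both arms inside each school. The term is undefined, and a treatment-effect variance can enter when schools are randomised within blocks; this trial uses two blocks of ten. A formula with both arms in each of 20 schools of 20 also misses 80%: 60–65% with 0.07 as a variance, 72–77% as an SD. The origin of the 80% remains unknown.

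A third is that only 16 students per school will be analysed (20 × 0.8). The Sample size section sets 25 as the target, so this is not the planned scenario.

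Finally, this is a pilot meant to give initial evidence, and nothing in the article says that a null result would be read as evidence against the programme. That bears on the consequences, not on whether the stated figure is right.

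**Conclusion.** The power statement is wrong as written. For 10 versus 10 schools with 20 students analysed in each, the printed inputs give about 56% (t, 18 df) to 60% (normal) two-sided power and 69–72% one-sided, all without baseline adjustment. Even with no clustering, two-sided power would be at most 77%. The shortfall is therefore 20–24 percentage points two-sided and 8–11 one-sided. The article specifies no df rule for its generalized linear model, so both reference distributions are given. The result assumes equal school sizes and d as a standardised mean difference. It does not establish the power of the baseline-adjusted analysis, which cannot be worked out from what is printed.

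**What to change.** 1. Restate the Sample size section for 10 versus 10 schools with 20 analysed per school: about 56–60% power at d = 0.27, and 80% power at d of about 0.36 (t, 18 df) or 0.34 (normal). Name the sidedness and the df assumption.
2. Define the variability of 0.07 and show how it enters a school-randomised calculation, or remove it.
3. If 80% rests on baseline adjustment, state the baseline–outcome correlation, the level (school, student or both) at which it acts, and whether d is on the raw or the change scale. With d = 0.27 in raw SD units, R² of about 0.37 (normal) to 0.44 (t) is needed if it acts equally at both levels, and more if at student level only.
4. Minor: use 25 per school as the recruitment target throughout, to match the stated 80% retention.

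This is a change of text. The stated power becomes less favourable unless a supported baseline correlation is supplied. Reporting the power correctly requires no extra schools.
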